#### 3.4.2. Clinical and cognitive assessments.

The clinical assessment (additional to MDS-UPDRS and NFOGQ used in the randomization) includes the PDQ-39: Parkinson’s Disease Quality of Life questionnaire, which has 39 questions reflecting 8 domains of quality of life. Subscale scores and a summary index representing the global health-related quality of life will be calculated. The PDQ-39 reflects limitations to participation in community mobility [52]. In addition, the Apathy Scale (AS) consisting of 14 items phrased to be answered on a four-point Likert scale [53] and the Geriatric Depression Scale (GDS) [54]; both recommended for use in PD [55,56], will be used as covariates in all analyses as apathy and depression may influence gait and turning [57]. The cognitive assessment includes *Executive function and* will be measured using Royall’s clock drawing (**CLOX 1**) and Trail-making (**TMT**) Part A and B [58]. Impaired executive function will use the cut-off of 2.5 on the Trail-making B/A [59,60]. *Global cognition* will be assessed with the Montreal Cognitive Assessment (**MoCA**) [61]. *Attention* will be measured with a computerized button pressing battery, involving simple (**SRT**) and choice reaction time (**CRT**) [62]. *Working memory* will be measured through seated forward digit span and *visuospatial ability* with a judgement of line orientation (**JLO**) tasks and Royall’s **CLOX 2** tasks.

#### 3.4.3. Cortical activity assessment.

A portable fNIRS system (Artinis Medical Systems) will be used to record cortical activity at 50 Hz. A neoprene head cap (fiber holder) marked with labels of the international 10–20 electroencephalography system and predetermined locations for the optodes will be placed on the participant’s head. Specifically, a 36-channel (26 + 10) arrangement with 6 short channels, consisting of 18 transmitters and 10 detectors/receivers, will cover PFC, SMA, primary motor, primary sensory and primary visual cortices bilaterally. Six short-separation channels will record superficial extracerebral hemodynamic response. *fNIRS* outcome measures while walking and turning (bilateral PFC, SMA, parietal and occipital cortical activity). Relative changes in the concentrations of HbO_2_ while walking or turning tasks will be compared to baseline conditions (e.g., standing); similar to our previous publications [36,63–65]. Briefly, the OxySoft (v3.7.2, Artinis Medical Systems) software preprocesses the NIRS signal by converting raw light intensity values to oxy-hemoglobin (HbO_2_), deoxy-hemoglobin (HHb), and total hemoglobin concentrations [66]. To eliminate equipment noise, respiration and heart pulsation, a low-pass filter with a cut-off frequency of 0.14 Hz will be applied to the fNIRS signal [67]. HbO_2_ and HHb concentrations will be calculated as the average of the channels from both sides of the skull that are located over specific cortical regions (PFC, SMA, primary sensory, and visual), which will be defined using 3D digitization. Only changes in HbO_2_ will be considered for further analysis, as HbO_2_ has been shown to be the more reliable and sensitive measurement than HHB [67]. Short-separation channel data will be regressed from the HbO_2_ signal to discount superficial extra-cerebral signal interference [36,63–65].

#### 3.4.4. Gait and turning assessment (Laboratory and Daily life).

Gait and turning measures are reported in Table 1 and calculated using a combination of proprietary algorithms (Mobility Lab V2 system, APDM Wearable Technologies, a Clario company) and custom algorithms validated by our Balance Disorders Laboratory [13,68,69].

**Table 1 pone.0336859.t001:** Primary and secondary outcomes.

Cortical activity (HbO_2_)	Gait measures	Turning measures
**Prefrontal**	Stride velocity (cm/sec) and CoV	# Steps to complete a turn
**Primary sensory**	Stride length (m) and CoV	Turn peak velocity (degree/s)
Supplementary Motor Area and primary motor	Stride time (s) and CoV	Turn duration (sec)
Primary visual	Local Dynamic Stability (LDS,-)	Turn trunk jerk (m^2^/sec^2^)

**Primary outcome in bold.**

In the laboratory, during walking trials, stride time variability (a key marker of automaticity) will be calculated as the coefficient of variation of stride time. Phase-dependent local dynamic stability (LDS) will be estimated using methods previously described in [40]. For the 360° turning in place task, we will analyze the yaw angular velocity from the posterior trunk sensor to compute [70] the average turning duration, number of steps in turn, and the average jerkiness of the turns.

#### 3.4.5. Daily Life mobility monitoring.

During the two-week home monitoring period, participants will wear two instrumented socks (one per foot) and a lumbar Opal sensor, secured with an elastic belt. These devices are to be worn for at least 8 hours/day during daily activities. The socks and lumbar sensor contain the same inertial measurement units as the standard Opals, including a tri-axial accelerometer, gyroscope, and magnetometer, sampling at 128 Hz. The sock design separates the battery (placed above the lateral malleolus) from the sensor (mounted on the foot dorsum), as detailed in [23,71–74]. The sensors are lightweight (22 g), store up to 30 days of data, and offer a battery life of approximately 12 hours.

Participants are instructed to remove and recharge the sensors nightly. Data are continuously recorded and stored locally on the devices, then returned by pre-paid mail after each week of monitoring. Upon receipt, the raw data are uploaded to a secure AWS cloud server, processed using validated algorithms, and results downloaded for analysis.

The algorithms used to calculate the measures of gait and turning were the same for the laboratory and daily life data, as were detailed previously [13,68,69]. In summary, the daily life algorithm first searches for possible bouts of walking from inertial sensor data from the feet using a time-domain approach. Second, individual steps are combined into potential bouts of walking if the duration from one step to the next step is less than 2.5 seconds. Finally, each possible bout that contains at least 3 seconds in duration and at least 3 steps is processed with the same gait algorithms included in Mobility Lab V2 (APDM Wearable Technologies, A Clario company) (20). For the gait measures reported in this paper, we calculated a mean and variability across all strides over the week of recording and included only the periods of straight walking. Straight walking were periods of walking in which the heading angle of the foot during stance changed by no more than 20 degrees during a single stride and that did not contain detected turns as determined from the lumbar sensor [74]. For turning measures, we used a previously published algorithm to detect and characterize each turn [74]. This approach ensured consistency in identifying turns across both structured lab settings and free-living conditions.

### 3.5. Intervention

#### 3.5.1. Device hardware.

The tactile cueing device was designed and manufactured in our laboratory. An individual device consists of four modules; two are worn on the instep of each foot, and the other two on each wrist (Fig 3). The module worn on the foot contains a microcontroller unit (MCU) with flash storage and an inertial measurement unit (IMU), while the module worn on the wrist contains an MCU and a vibration motor. The wrist and foot modules communicate via Bluetooth Low Energy (BLE). The IMU samples at 104 Hz and the vibration motor is driven at 170 Hz.

**Fig 3 pone.0336859.g003:**
[figure not shown]
Tactile cueing device. Participants will use 2 IMUs (R and L foot), and 2 vibrotactile units (R and L wrist). In the personalized cueing mode, the wrist receives tactile stimulation when the ipsilateral foot is in the stance phase. The inertial sensors (IMU) identify the stance phase for each foot (red color) during the gait cycle. The picture to the right shows the IMUs and vibrotactile units. In the fixed cueing mode, tactile stimulation will occur at a set frequency based on the person’s gait speed – measured during the laboratory visit. R = Right, L = Left. The IMUs of the cueing device are independent of the IMUs for Home monitoring.

All participants will receive this identical sensor hardware, capable of operating in either personalized (closed-loop) or fixed (open-loop) cueing mode based on group allocation (Fig 3).

In the laboratory, the immediate effects of cueing will be evaluated following a 15-minute acclimatization period using fNIRS and wearable sensors.

After Laboratory Visit 1, participants will begin the home monitoring phase. During week 2 of this phase, they will be instructed to use the cueing system for at least 30 minutes per day when they feel in their best ON medication state. Participants will be able to divide the 30 minutes into shorter periods as needed in relation to fatigue, space or other issues. Additionally, we will ask to participants to maintain their medication schedule and refrain from any change in medication or exercise for the duration of the trial.

For both the laboratory visit and home use, the cueing intervention will be stopped if the patients report intolerable discomfort, balance issues, or if they experience an adverse event, such as a fall or other important health problem.

The intensity of the intervention and hardware setup will be the same across both groups.

The personalized cueing (closed-loop) is triggered by the individual’s angular velocity of the foot in real-time and delivers tactile stimulation to the ipsilateral wrist during the stance phase of gait. This modality is personalized and real-time to each step made by the individual (Fig 3).

The fixed cueing (open-loop) delivers tactile stimulation at a frequency matched to the individual’s average gait cycle time, determined during the in-lab portion of their visit using the Mobility Lab V2 algorithms. This value is used to as an input to the vibrotactile device to provide alternating vibration to the left and right wrists that is consistent with the person’s self-selected walking speed. Viewing individual time points of the gait cycle as a percentage of the full duration, vibration will be provided to the left wrist between 5%−45% and vibration to the right wrist will occur between 55%−95%. The vibration will be off outside of these windows, and the pattern will repeat after a gait cycle is completed.

#### 3.5.2. Adherence monitoring.

Participants will receive a printed diary to record the times they put on and removed the sensor each day, along with the timing of their medication and any use of the cueing device. Additionally, when the sensors are returned, we will download data that includes precise timestamps. The cueing device also automatically logs usage times, providing an accurate record of when it was activated.

#### 3.5.3. Stopping rules.

This study will be stopped prior to its completion if: (1) the intervention is associated with adverse effects that call into question the safety of the intervention; (2) difficulty in study recruitment or retention will significantly impact the ability to evaluate the study endpoints; (3) any new information becomes available during the trial that necessitates stopping the trial; or (4) other situations occur that might warrant stopping the trial.

### 3.4. Outcome measures

Primary and secondary outcome measures are summarized in Table 1, which includes the domains and metrics. These measures have been selected based on 1) potential relation to gait automaticity (PFC activity and gait variability) and 2) response to cueing (stride time, LDS, turn duration, turn jerkiness).

Effects of personalized versus fixed tactile cueing during daily life will also be explored via cortical, gait and turning outcomes in Table 1 during week 2 of cueing feasibility at home versus week 1. Daily life gait and turning metrics are exploratory.

Analyses will be performed on an intention to treat basis. However, for the home monitoring, we will exclude participants who will not use the sensors for at least 5 hours per day and 5 days per week. For the cueing intervention, we will exclude participants if they walk with cueing for less than 20 minutes per day or less than 5 days per week.

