#### 3.5.2. Statistical analysis.

The primary outcome will compare PFC and sensory cortex HbO2 while walking and turning between personalized tactile cueing and fixed tactile cueing groups measured during Laboratory Visit 1, without and with cueing. We will average the HbO2 concentrations over 2-minutes of walking (and over 1-minute of 360-degree clockwise and counterclockwise turning), then compare within-subject effects (baseline versus cueing) and between-subject effects (personalized versus fixed cueing) in a repeated measures analysis. Specifically, we will apply mixed-effects models with HbO2 levels (averaged over walking bout) for each person at each assessment time point as the dependent variable. We will include as independent variables: (i) indicator variable for group assignment (personalized or fixed cueing), (ii) indicators for time points (baseline, cueing), and (iii) group by assessment interaction terms. Randomization stratification variables, Hoehn and Yahr, FOG and cognitive status, will be entered into the model as covariates. A random subject intercept will account for correlation between the two repeated measurements within each subject.

Similar linear mixed effects models will be used to demonstrate improvement in walking and turning metrics in the laboratory (carried out with the fNIRS measurements), secondary outcomes. Significance level will be set at 0.05 for testing whether coefficients are different from 0 for primary and secondary outcomes.

We will employ similar linear mixed effects models to investigate whether the two cueing modalities will result in different improvements of walking and turning during daily life. This is an exploratory analysis. For the week of daily mobility without and with cueing, we will summarize walking and turning measures at home (outlined on Table 1) by computing the average over 7 days of daily activity, considering only the recordings with more than 7 hours per day and at least 5 days (Table 1). Randomization stratification variables, Hoehn and Yahr, freezing of gait and cognitive status, will be entered into the model as covariates. Additional covariates would be the life space assessment and activity levels. The effect sizes from models fit for this pilot study will be used to determine the number of subjects required for a future clinical trial.

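### The exploratory home comparison drops randomised participants for low cue use, states no all-randomised counterpart, and rests on two incompatible sensor-wear thresholds

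*Protocol article*

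**What the plan says.** Section 3.4 (Outcome measures) opens with the general principle: "Analyses will be performed on an intention to treat basis". It then sets the home phase apart with two exclusions. The first concerns sensor wear: "we will exclude participants who will not use the sensors for at least 5 hours per day and 5 days per week". The second concerns cue use: "we will exclude participants if they walk with cueing for less than 20 minutes per day or less than 5 days per week".

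Section 3.5.2 (Statistical analysis) describes the weekly home summaries and applies a different wear limit: "considering only the recordings with more than 7 hours per day and at least 5 days". It also states the status of this comparison: "This is an exploratory analysis".

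Participants are asked for more than any of these thresholds. On sensors, section 3.4.5 says: "These devices are to be worn for at least 8 hours/day during daily activities". On cueing in week 2, section 3.5.1 (Device hardware) tells them to "use the cueing system for at least 30 minutes per day". That section also provides that "the cueing intervention will be stopped if the patients report intolerable discomfort, balance issues, or if they experience an adverse event".

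Sections 3.5.1 (Power analysis) and 3.5.2 (Statistical analysis) both say that estimates from this pilot will feed the sample size of a larger trial.

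**The concern.** Two separate matters meet in the home analysis set.

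The first is the cue-use exclusion. Minutes of cueing are recorded in week 2, after allocation, and only after participants have tried their assigned mode. If one mode is less comfortable or less helpful, its users may use it less and leave the comparison in larger numbers. The modes would then be compared among people who got on with them, which is no longer the randomised comparison. Losing more poor responders from one arm flatters that arm. A later trial analysed on all randomised participants could be mis-sized from such an estimate. Non-users are also part of the feasibility answer that the exploratory objective in section 2 asks for.

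The second is the wear threshold. Two limits govern the same recordings, so the article does not fix one analysis set.

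**Working it through.** **The plan's own figure.** The documents give no adherence or wear rates. The only stated margin for exclusions is in section 3.5.1 (Power analysis): 36 patients needed, 60 recruited, so 1 − 36/60 = 40% could be lost. That rests on 81.2% power for 0.50 SD, alpha 0.02 and covariate R² 0.20. For two equal arms, λ = N f²/(1 − R²) with 1 and N − 3 degrees of freedom:

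- f = 0.50: λ = 36 × 0.25/0.80 = 11.25, power 81.3%. But f = 0.50 is a difference of 1.0 SD.
- A 0.50 SD difference is f = 0.25: λ = 36 × 0.0625/0.80 = 2.81, power 23.7%.

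The figure reproduces only for a difference of 1.0 SD. That is a separate matter; here it means that the 40% margin cannot be relied on to absorb exclusions at 0.50 SD.

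**The wear rules side by side.**

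| Daily wear, on at least 5 days | Section 3.4 (Outcome measures) | Section 3.5.2 (Statistical analysis) |
|---|---|---|
| 4 h | excluded | not used |
| 6 h | kept | not used |
| 8 h | kept | used |

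Reading one rule as applying to participants and the other to recordings does not reconcile them: at 6 hours every day, a participant stays in the set with no usable recording. As an illustration only, take daily wear as normal with mean 7 to 9 hours and between-person and within-person SDs of 1.5 or 2 hours, over one 7-day week. The 5-hour rule then keeps about 43 to 59 of 60 and the 7-hour rule about 23 to 49. The choice moves roughly 10 to 26 participants.

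**What selection on cue use can do.** The planned model has group, time (without and with cueing) and their interaction. With both weeks observed, the interaction estimates the between-arm difference in mean change, week 2 minus week 1.

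- If use depends on a stable trait S that shifts both weeks by the same amount bS, the change is (… + bS) − (… + bS), and S drops out. Selection on stable severity then leaves this contrast essentially unbiased.
- If use depends on the change itself, selection does not drop out. Let latent adherence correlate ρ with the change, with a share e excluded in an arm and c = Φ⁻¹(e). The mean among those kept shifts by ρ φ(c)/(1 − e), and the spurious difference is that term for one arm minus the other.

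Example with ρ = 0.3 and exclusions of 10% and 30%: 0.3 × (0.497 − 0.195) = 0.091 SD. Assumed values throughout, no true effect, in SD of the change:

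| ρ | 10% v 10% | 10% v 30% | 10% v 40% | 20% v 40% |
|---|---|---|---|---|
| 0.2 | 0 | 0.060 | 0.090 | 0.059 |
| 0.3 | 0 | 0.091 | 0.135 | 0.088 |
| 0.5 | 0 | 0.151 | 0.224 | 0.147 |

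The extreme case for losing 15% of one arm, with exactly the worst responders removed and nobody lost from the other arm, is φ(1.036)/0.85 = 0.27 SD.

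**The case against.** The strongest defence is that nothing confirmatory is at risk. Daily-life outcomes are labelled exploratory throughout, and the primary and secondary outcomes are measured at Laboratory Visit 1, before any home wear or home cueing. The exclusions are written openly as an exception to intention to treat. Those analysing the data are kept blind to arm (sections 3.1 and 3.3), and an all-randomised sensitivity analysis might sit in a fuller document.

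Most of this stands, and it rules out several stronger readings that a reader might infer:

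- *The trial's main result is compromised.* It is not; neither rule touches Visit 1 data.
- *A per-protocol analysis is passed off as intention to treat.* The exception is declared.
- *Everyone whose cueing is stopped disappears.* Not necessarily; someone stopped after five qualifying days still passes.
- *The set can be picked to favour one arm.* Blinding limits that. If both wear rules are applied literally, the stricter one decides, so the set is inconsistently specified rather than absent.
- *A bias of 0.27 SD, over half of the 0.50 SD target, is to be expected.* That figure needs perfect dependence of use on response in one arm only, which nothing in the documents supports. It is also in units of the change, whereas the target is stated for the measures themselves.
- *Severity-related adherence alone biases the result by 0.03 to 0.08 SD.* Figures of that order arise when raw week-2 levels are compared. They largely cancel in the planned week-2 versus week-1 model, which also adjusts for Hoehn and Yahr stage and freezing.

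What does not stand is deferring the matter to another document. The article itself fixes two conflicting thresholds, and makes the adherence-restricted set the only home analysis it describes.

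**Conclusion.** The point holds, at the level of should-fix. Two facts rest on the text alone: the home comparison excludes randomised participants for behaviour observed after allocation that may depend on the assigned mode, with no all-randomised analysis stated beside it; and the two wear thresholds cannot both govern the same data.

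The size of any bias cannot be derived from the documents. It arises mainly if cue use depends on the response to cueing and exclusion differs by arm. The 0.06 to 0.22 SD range assumes correlations of 0.2 to 0.5 and exclusion of 10–20% in one arm against 30–40% in the other; for comparison, the unadjusted standard error at 30 per arm is √(2/30) = 0.26 SD. The practical harm is to the planning estimate for the next trial and to the feasibility message.

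**What to change.** - State one wear-time rule, identically in sections 3.4 (Outcome measures) and 3.5.2 (Statistical analysis), fixed before unblinding. Keep the other threshold as a sensitivity analysis. Say whether the rule applies to each week separately.
- Make the main home comparison all randomised participants whose sensor data meet that rule, in their assigned group, whatever their cue minutes. Some wear rule is needed to compute the outcome at all; a cue-use rule is not.
- Label the 20-minute/5-day set a per-protocol sensitivity analysis.
- Report the share failing each rule, by arm, as a feasibility result.

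The cost is wording in two sections and one more analysis. Sensor timestamps and device-logged cue use are already collected (section 3.5.2, Adherence monitoring), so no new data are needed. The downside is that the all-randomised effect may be smaller than the effect among adherers.

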### 3.5. Statistical methods

#### 3.5.1. Power analysis.

We computed power to detect differences in a larger reduction of PFC activity during personalized, compared to fixed, tactile cueing. Furthermore, we predict that personalized cueing will show less activation of PFC versus fixed cueing (i.e., more automatic). We conservatively assume 54 subjects, 27 for each group (personalized and fixed training), will be included in this analysis, based on recruitment of 60, and allowing for modest dropout (> 10%). We computed power for a repeated-measures ANOVA model with 1 between and 1 within subject effect based on the Geisser-Greenhouse F-test (equivalent to a mixed model). Using patterns of HbO2 levels comparable to previously published results(ref Stuart and Mancini JNPT), assuming between-subject variance of 0.08, modest intra-subject correlation of 0.2, and level of significance at 0.05, we find that power is 82% for the test of between-subject effects (cueing group comparison), and 94% for the test of interaction (differential impact of dual-task versus single-task walking between the personalized- and fixed-cueing groups).

We also computed sample sizes required to achieve at least 80% power for detecting group differences of at least 0.50 SD for measures of walking and turning in daily life with ANCOVA models, conservatively assuming covariate R2 equal to 20%. We set level of significance to 0.02, which is the average alpha level when employing the Holm correction method over 6 outcomes (see below). Under these assumptions, 36 patients (18 per arm) are required to achieve 81.2% power. Thus, our plan to recruit 30 per arm will result in adequately-powered tests while allowing for missing/insufficient data or patient dropout. One of the goals of this trial is to generate preliminary estimates of sensitivity of daily life gait and turning quality due to a cueing intervention. These estimates ultimately will be used to inform power and sample size computations for a larger clinical trial. The small intervention proposed here (30 per group) is not designed to be a highly powered trial itself, but will make use of a randomized, two-group intervention design. All computations were conducted using PASS v15 (PASS 15 Power Analysis and Sample Size Software (2017), NCSS, LLC).

We are not planning interim analysis, and we are not expecting to stop the recruitment early.

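### The stated 82% and 94% power belong, as written, to a model with task as the within-subject factor, so the planned group-by-time test on PFC activity has no stated power

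*Protocol article*

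**What the plan says.** The Power analysis section (the second section numbered 3.5.1 in the protocol article) opens with the aim: "We computed power to detect differences in a larger reduction of PFC activity during personalized, compared to fixed, tactile cueing". On sample size it says: "We conservatively assume 54 subjects, 27 for each group (personalized and fixed training), will be included in this analysis". It then describes the method: "We computed power for a repeated-measures ANOVA model with 1 between and 1 within subject effect based on the Geisser-Greenhouse F-test". The inputs are given as "assuming between-subject variance of 0.08, modest intra-subject correlation of 0.2, and level of significance at 0.05", with HbO2 patterns taken from a published study and no means printed. The result is that "power is 82% for the test of between-subject effects (cueing group comparison), and 94% for the test of interaction", and the interaction is explained in parentheses as "differential impact of dual-task versus single-task walking between the personalized- and fixed-cueing groups".

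The Statistical analysis section that follows specifies a mixed model for HbO2 with an indicator for group and then "ii) indicators for time points (baseline, cueing), and (iii) group by assessment interaction terms". Hoehn and Yahr stage, freezing status and cognitive status are covariates. A random intercept per participant covers two repeated measurements. Neither task nor a group-by-task interaction appears among the model terms.

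**The concern.** The stated aim concerns a difference between arms in the change from uncued to cued walking. In the planned model that is the group-by-time term. A power model with a single within-subject factor cannot hold both task and time. If that factor is task, as the parenthesis says, the 94% belongs to an interaction that the analysis does not fit.

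The 82% does not carry over either. In the power model the group comparison averages over single- and dual-task walking. In the planned model the group main effect averages over baseline and cueing, and randomized arms have no expected difference at baseline.

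At stake is whether the figures offered in support of 54 analysable participants describe the test on which the primary PFC conclusion will rest.

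**Working it through.** **Inputs.** From the Power analysis section: n = 27 per arm, variance s² = 0.08, correlation ρ = 0.2, α = 0.05. Assumptions of this check: two-sided testing, two levels of the within-subject factor (so the Geisser-Greenhouse correction equals 1), and 0.08 as the variance of one measurement, giving SD = √0.08 = 0.283. Power is from the noncentral t distribution with 52 degrees of freedom.

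**Step 1: the plan's own figures.** Without the means, power cannot be computed forward, so the differences were back-solved.

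- Group comparison averaged over the two levels: SE = √[s²(1+ρ)/2 × 2/27] = √(0.048 × 0.0741) = 0.0596. A difference of 0.175 (0.62 SD) gives 82.1%.
- Interaction (difference of differences): SE = √[2s²(1−ρ) × 2/27] = √(0.128 × 0.0741) = 0.0974. A difference of 0.35 (1.24 SD) gives 94.1%.

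Both printed figures are reproduced. The second difference is twice the first (a ratio of about 1.96 to 2.03 once rounding of 82% and 94% is allowed for). This is the pattern of arms that are equal in one condition and 0.35 apart in the other: the average gap is 0.35/2 = 0.175 and the difference of differences is 0.35. The results in SD units do not change if 0.08 is read as an SD or as a between-subject variance component.

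**Step 2: if the powered factor was really baseline/cueing.** Arms equal when uncued and 0.35 apart when cued is what a randomized design would suggest. The interaction in Step 1 is then group-by-time, and its power is 94%.

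**Step 3: if the powered factor was task, as printed.** The documents give no group-by-time effect, so only scenarios are possible. Group-by-time power with 27 per arm and a baseline-cueing correlation of 0.2:

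| Difference in change (SD) | Power |
|---|---|
| 0.4 | 21% |
| 0.5 | 30% |
| 0.6 | 40% |
| 0.8 | 63% |
| 1.0 | 81% |
| 1.2 | 93% |

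For a difference in change of 0.175, by baseline-cueing correlation, with SE = √[2s²(1−ρ) × 2/27]:

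| Correlation | SE | Power |
|---|---|---|
| 0.2 | 0.0974 | 42% |
| 0.5 | 0.0770 | 61% |
| 0.7 | 0.0596 | 82% |
| 0.8 | 0.0487 | 94% |

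**Step 4: why 82% is not the group main effect of the planned model.** If the arms are equal at baseline and 0.175 apart at cueing, the averaged group difference is 0.175/2 = 0.0875. With SE 0.0596 (ρ = 0.2), power is 30%. This too depends on an assumed effect.

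**The case against.** The strongest reply is that only the parenthesis is wrong. The opening sentence of the Power analysis section speaks of a larger reduction, and the back-solved pattern suits a baseline/cueing factor at least as well as a task factor. On that reading the planned test has 94% power and the calculation is sound. This cannot be excluded. It leaves the printed description wrong and in need of correction, and only the sponsor can say which factor was used.

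A second reply is that the powered response was already the change from baseline to cueing. The 82% would then be a group comparison of change averaged over the two tasks. The section speaks of HbO2 levels, which counts against this, and the planned model has no task term through which to form that average.

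A third reply is that this is a pilot. The remark that the trial is not meant to be highly powered follows the daily-life calculation, whereas for PFC activity the section claims specific power. It is true, though, that 54 was not derived from the 82%. It comes from recruiting 60 and losing about 10% (60 × 0.9 = 54), with power then computed at that number.

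Two stronger conclusions are tempting. A reader might infer that the primary test is underpowered. The documents do not show this, because the low figures in Step 3 rest on effects and correlations that the plan does not state. A reader might also infer that the plan assumes no group effect in single-task walking. No means are printed, and the zero cell is a back-solution that could equally be the uncued baseline.

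**Conclusion.** The point holds as a mismatch between two adjacent sections: they name different within-subject factors, so as written neither 82% nor 94% is the power of the group-by-time test on PFC HbO2. That power is 94% if the factor was mislabelled. Otherwise it is unstated, with scenarios from 21% to 93% for effects of 0.4 to 1.2 SD at a correlation of 0.2, and higher at a given effect if baseline and cueing measurements correlate more strongly. The mismatch itself rests on the text alone. The back-solved differences and the scenarios rest on the assumptions listed in the check. What is shown is that the stated power is not tied to the planned test. It is not shown that the printed figures are arithmetically wrong or that the sample is too small.

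**What to change.** In the Power analysis section, state which within-subject factor was powered. Print the assumed HbO2 mean for each arm and condition, from the sponsor's own calculation, together with the baseline-cueing correlation. Replace the 82% and 94% with the power of the group-by-time contrast on PFC HbO2 at 27 per arm. If the group-by-task interaction is meant to be tested, add task and its interactions to the walking model in the Statistical analysis section. Otherwise remove that power figure.

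The cost is a recalculation and revised wording, with no extra participants or data. The downside is that the restated power may be less favourable. A primary contrast averaged over single- and dual-task walking and adjusted for baseline would be an optional design choice. It changes what is estimated and is not needed to repair this defect.
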